### **2.2.2 Interventions**

The MT approach in this study is informed by models previously described and tested [18, 21, 25, 26]. Like other MT models [26], it is based on the notion that infants have a capacity to communicate actively [27, 28]. As in some newer models, parents are actively involved and empowered [21, 29]. The approach here thus builds on an emerging consensus, but is more explicit in its adaption to developmental levels and emphasis on infant/parent co-regulation. Furthermore, unlike previous studies [25], MT is extended beyond the tertiary care setting to help with the transition to daily life and municipal care. MT focuses on supporting positive relationship formation within the infant/parent dyad by promoting beneficial co-regulation, and includes psychosocial support of the parent.

**MT during NICU:** Participants will be offered individual MT sessions 3 times/week for 20-30 minutes/session, with a maximum of 36 sessions per infant (assuming a maximum NICU stay of 9 weeks). NICU-MT will be provided for all eligible infants once they achieve medical stability, usually after 26 weeks postmenstrual age (PMA; defined as GA at birth plus the time since birth [30]). A flexible protocol of procedures matched to infant PMA, familial/cultural preferences, and infant's demonstrated readiness to receive stimulation, will occur as individually-tailored sessions at bedside:

*Approximately 26 to 31.99 weeks PMA – Cautious use of sung/toned voice:* The music therapist shows caregivers how to use facilitated tucking and midline alignment (if appropriate for the infant) along with

[figure not shown]

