### 2.2.3 Outcomes

Outcomes will be assessed at several time points: at baseline; one to two days before discharge to home; at 6 months corrected age (end of MT; primary endpoint); and 12 months of corrected age (CA; chronological age reduced by number of weeks born preterm [30]). Data collectors and assessors will be trained in assessment procedures and blinded to participant allocation; success of blinding will be verified.

**Primary outcome: Bond between primary caregiver and infant** will be evaluated at all time points (**primary time point: 6 months CA**) using the Postpartum Bonding Questionnaire (PBQ). PBQ is a self-rating screening instrument for disorders of the early mother-infant relationship consisting of 25 statements on a six-point Likert scale (each 0-5; sum score ranging from 0 to 125; high = problematic), addressing problems in the mother-infant relationship based on weakened bonding; rejection and anger; anxiety about care; and risk of abuse [32]. The scale is validated and widely used in clinical practice and research [33]. It has been translated and tested in several languages and cultures [34] and has high internal consistency [35] and test-retest reliability [32], also in the Norwegian version [36].

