**Power calculation and sample size:** No previous RCT examined effects of MT on the PBQ; two small RCTs included in our systematic review [25] and a recent non-randomized study [29] examined mother-infant bonding, but provided insufficient data for meta-analysis. Studies using the PBQ with other interventions found effects ranging from around 0.25 ([44], posttest) through 0.5 ([45], mothers at 1/6 months), 1.4 ([46], 4 months), 2 ([45], fathers at 1/6 months), 9 ([44], 3 months), with SDs ranging from 4 to 12. Assuming a difference of 4 points on the PBQ ( $SD = 8$ ) as a minimal clinically important difference for this study, power of 80% will be achieved for each main effect (each tested on a two-sided 2.5% significance level, i.e. 5% with Bonferroni correction for two tests) with a sample size of 155. Taking into account some clustering by country (ICC 0.01; 5 countries), this is increased to 203. To allow for 20% attrition, we will aim to include 250 infants (50 in each country) and their parents. This sample size will also ensure power for testing proportion differences of about 15% (e.g. binary analysis of problematic bonding; re-hospitalization). Special considerations are needed for multiple pregnancies (twins, triplets, etc.), which account for about 2% in Hordaland [4], but are more common in NICUs due to their elevated risk of preterm birth. Including all siblings would serve to increase the sample size, but may lower the resulting power due to cluster effects.

Therefore, we will only formally enroll and analyze the first-born sibling of each multiple pregnancy, although all will receive the intervention.

**Data analyses:** All randomized participants will be included in the main analysis (intention-to-treat). Descriptive statistics will characterize basic properties of the sample and provide information for power calculation for the multi-center study. Effects will be examined by testing the randomized groups for differences in the primary endpoint (t-test or Mann-Whitney; change in PBQ scores to 6 months CA), as well as by fitting linear mixed models. In the first modeling step we will assess the effect of the first randomization (Fig. 1) using the following model:

$$PBQ_{it} = \beta_0 + \beta_1 time_t + \beta_2 gr_i + \beta_{12} time_t gr_i + U_i + \varepsilon_{it} ,$$

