where  $PBQ_{it}$  denotes the PBQ score for participant  $i$  at measurement  $t$ ,  $time_t$  the time from baseline at measurement  $t$  and  $gr_i$  the randomization group of participant  $i$ .  $\beta_0$ ,  $\beta_1$ ,  $\beta_2$  and  $\beta_{12}$  are the coefficients estimated in the model,  $U_i$  is an individual random term per participant and  $\varepsilon_{it}$  an independent, identically distributed error term. In the second step we refine the model to take into account both randomization steps, leading to the extended model:

$$PBQ_{it} = \beta_0 + \beta_1 time_t + \beta_2 grR1_i + \beta_{12} time_t grR1_i + \beta_3 grR2_i + \beta_{13} time_t grR2_i + U + \varepsilon_{it} ,$$

with the same notation as above and  $grR1_i$  and  $grR2_i$  denoting the groups from the first and second randomization, respectively. In these models  $\beta_1$  describes a group-independent time effect,  $\beta_2$  and  $\beta_3$  a time-independent group effect, and  $\beta_{12}$  and  $\beta_{13}$  the time-dependent change of the group effect. We will investigate both linear and simple contrasts (comparing each time point with the baseline) in time to assess the treatment effect. The same analyses will be done for the secondary outcomes; using an analogous generalized linear mixed model for binary outcomes. Per-protocol analyses will include those who received at least 6 MT sessions in the NICU and at least 5 MT sessions post-discharge, respectively; these are considered the minimum numbers for the intervention to be successful. Additionally, we will conduct exploratory statistical analyses for prespecified subgroups (sex; GA at birth [ $<28$  wks, 28 to  $<32$  wks, 32 to  $<35$  wks]; hearing status at discharge [normal vs. abnormal]; bonding at baseline [PBQ impaired bonding score  $\geq 11$  vs.  $<11$ ]) as well as qualitative/mixed-methods analyses of process data to maximize learning.

**Data management plan:** To promote transparency and applicability of trial results and to facilitate re-analysis by other researchers while also protecting anonymity, de-identified individual patient data will be made available through the Norwegian Centre for Research Data (NSD).

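### The mixed model's random intercept with independent errors can misstate the standard errors of change over time, mainly for the linear slope, and the plan should use an unstructured covariance

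*Combined protocol and SAP*

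**What the plan says.** In section 2.2.4 (Data analyses), the first mixed model contains time, group and their product. It also has a term U that "is an individual random term per participant and" an error described as "an independent, identically distributed error term". The second model adds the second randomization and keeps the same notation. Its U is printed without a subscript, and I read it as the same random intercept. No random slope, serial correlation, visit-specific variance, unstructured covariance or robust standard error is mentioned anywhere.

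Section 2.2.3 lists the visits as "baseline; one to two days before discharge to home; at 6 months corrected age (end of MT; primary endpoint); and 12 months of corrected age". The primary time point is 6 months CA.

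Treatment is judged from the group-by-time terms: "We will investigate both linear and simple contrasts (comparing each time point with the baseline) in time to assess the treatment effect". The primary endpoint is also tested directly: "t-test or Mann-Whitney; change in PBQ scores to 6 months CA), as well as by fitting linear mixed models". Each main effect is "each tested on a two-sided 2.5% significance level, i.e. 5% with Bonferroni correction for two tests". Secondary outcomes are to have the same analyses, with a generalized linear mixed model for binary ones.

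**The concern.** A random intercept with independent errors implies compound symmetry: the same variance at every visit and the same correlation between every pair of visits. Baseline and discharge are separated by a NICU stay (section 2.2.2: "assuming a maximum NICU stay of 9 weeks"), whereas baseline and 12 months CA are more than a year apart. The model treats both pairs as equally correlated.

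The standard error of a group-by-time contrast depends directly on this assumption. The model pools all within-participant variation into a single figure and applies it to every contrast. If correlation falls with time, contrasts over long intervals get a standard error that is too small and those over short intervals one that is too large. At stake are the p-values and confidence intervals of the model's treatment contrasts.

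**Working it through.** **The plan's own figures.** The plan states no correlation and no false-positive rate for the mixed model, so there is none to reproduce. Its sample size does reproduce, as a plain two-group comparison: n per arm = 2 × 8² × (2.2414 + 0.8416)² / 4² = 76.04, so 77 per arm and 154 in total. The exact noncentral t gives 155. The sample size therefore rests on a two-group comparison with no repeated-measures covariance.

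**Inputs.**
- From the documents: four visits, random intercept, independent errors, two-sided 2.5% per main effect (critical value 2.2414), 1:1 allocation.
- Assumed: visit times t = (0, 2, 9, 15) months, the within-participant covariance matrix S, and complete data.

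**Formulas.** With complete data the model's within-participant variance is s² = (tr S − 1′S1/4)/3. For a contrast c the model uses s²·c′c, while the true variance is c′Sc. The group-size factor is common to both and cancels. With R = c′Sc/(s²·c′c), type I error = 2 × (1 − Φ(2.2414/√R)).

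**Worked case: correlation 0.7 per visit, unit variance.**
- tr S = 4 and 1′S1 = 4 + 2 × (3 × 0.7 + 2 × 0.49 + 0.343) = 10.846, so s² = (4 − 2.7115)/3 = 0.4295.
- 6 months vs baseline: true 2 − 2 × 0.49 = 1.020; model 2 × 0.4295 = 0.859; R = 1.187. The standard error is 8% too small and type I error is 4.0%.
- 12 months vs baseline: true 2 − 2 × 0.343 = 1.314; R = 1.530; type I error 7.0%.
- Discharge vs baseline: true 2 − 2 × 0.7 = 0.600; R = 0.698; type I error 0.7%.
- Linear slope: centred times (−6.5, −4.5, 2.5, 8.5), sum of squares 141. True 104.64; model 0.4295 × 141 = 60.56; R = 1.728. The standard error is 24% too small and type I error is 8.8%.

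**The same formula over a range of covariances (nominal 2.5%).**

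| Assumed covariance | Linear slope | 12 months vs baseline | 6 months vs baseline | Discharge vs baseline |
|---|---|---|---|---|
| Compound symmetry | 2.5% | 2.5% | 2.5% | 2.5% |
| Person + serial + noise (0.4/0.4/0.2, 0.5/0.3/0.2, 0.5/0.2/0.3; decay 0.90 or 0.95 per month) | 4.0–6.3% | 3.3–4.3% | 2.6–2.9% | 0.6–1.6% |
| Pure serial decay (0.6–0.8 per visit; 0.90–0.97 per month) | 7.9–12.3% | 6.1–7.9% | 3.0–4.0% | below 1% |

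Under pure decay the discharge-versus-baseline standard error is 17% to 95% too large. With four visits R cannot exceed 3, so 19.6% is a ceiling for any contrast. Tripling 2.5% to 7.5% needs R = 1.58, a standard error about 21% too small.

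**Simulation check.** 10,000 null trials were run with N = 200, visits at 0, 2, 8.5 and 14.5 months, and six covariances. At serial correlation 0.9 per month the linear slope had 9.7% error, against 9.9% from the formula at those times. The t-test on 6-month change stayed at 2.2% to 3.0% throughout.

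**The case against.** The strongest reply is that the primary inference is sound. The planned t-test or Mann-Whitney on 6-month change uses its own variance and ignores the model's covariance; with complete data it holds its level. That stands. What remains is that the plan sets the mixed model beside that test without saying which decides, and the mixed model is the only described analysis that uses all visits and enters both randomizations together.

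A second reply is that no document shows compound symmetry to be wrong. That also stands: under compound symmetry every contrast is exactly nominal. The standard errors can be wrong; they are not shown to be wrong.

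Four stronger readings are tempting but unsupported:
- **The trial's false-positive rate triples.** Tripling concerns the linear slope, and needs strong serial decay or a large spread of individual slopes. With a stable person effect and measurement noise, both plausible for a self-report scale, the slope stays at about 4% to 6%. The 6-month model contrast never approaches tripling.
- **All the model's p-values are too optimistic.** Discharge versus baseline becomes conservative when correlation falls. Under a random slope or changing variances, even the 6-month contrast can fall slightly below nominal (1.8% at the lowest).
- **Every secondary scale is affected.** The text gives no visit schedule per scale, and the flow chart that carries it is not shown in the copy reviewed. A change between only two visits does not have this problem, and re-hospitalization is binary.
- **Uneven spacing is itself the fault.** Time enters as actual time from baseline. Uneven spacing only makes a common correlation less plausible.

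**Conclusion.** The point holds in a limited form. The specified covariance is a special case that the plan neither justifies nor backs with an alternative, and the contrasts it governs are the model's stated treatment tests. If correlation falls with time, the linear slope is the contrast most exposed and 12 months versus baseline is next. The primary 6-month contrast is only mildly inflated, and discharge versus baseline loses power. Secondary scales measured at three or more visits share the issue.

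All the error rates rest on assumed visit times and covariances and on complete data; the effect of attrition was not assessed. Moving the visits to 0/1/7.5/13.5 or 0/3/10/16 months does not change the picture: under pure decay the slope runs from 7.7% to 13.0% over the visit times tried. This is a worthwhile and inexpensive correction to the model specification. It does not undermine the 6-month t-test.

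**What to change.** Before any unblinded analysis, specify the repeated-measures model with visit as a category, group-by-visit terms for each randomization, an unstructured within-participant covariance (10 parameters for four visits) and Kenward-Roger degrees of freedom. State whether this model or the test of 6-month change is decisive.

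Prespecify a fallback for non-convergence that suits uneven spacing, for example continuous-time serial correlation plus a random intercept with visit-specific variances, with robust standard errors. A Toeplitz structure would not suit: it gives baseline–discharge and discharge–6 months the same correlation despite their very different intervals.

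If the linear trend is kept, label it exploratory and include a random slope or robust standard errors. Apply the same rule to secondary scales with three or more visits.

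The cost is a few more covariance parameters and slightly fewer degrees of freedom, with about 200 families expected after attrition (250 × 0.8). No extra participants, visits or data are needed. The replacement models were not themselves simulated here.

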#### **2.2.4 Trial procedures, statistical considerations, and data management**

**Randomization, allocation concealment and blinding:** After informed consent and baseline assessment, participants will be randomly assigned to NICU-MT or standard care using a computer-generated randomization list, with ratio 1:1, in blocks with sizes of 2 or 4 varying randomly, using email and an online system. The random allocation sequence will be generated and administered by people with no involvement in the clinical work to ensure allocation concealment. One day before discharge to home, participants will be randomized a second time to post-discharge MT or standard care in a 1:1 ratio, using the same procedures. This two-step randomization was chosen as the best way to create balance among those remaining in the study for the aftercare phase, and to avoid differential drop-out in the NICU phase due to expectations for the aftercare phase. In multiple pregnancies, only the first-born infant will be included and randomized, while remaining siblings will receive the same interventions for ethical and practical reasons. Blinding of interventions is not possible, but all outcomes that are not self-reports will be blinded, and success of blinding will be tested.

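### The extended mixed model gives the second randomization an effect at baseline and discharge, where it should be zero; with linear time the 6-month estimate then depends on the later course of the effect (30–34% too small if it is sustained), and the unbiased contrasts lose precision

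*Combined protocol and SAP*

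**What the plan says.** Section 2.2.4 (Data analyses) plans a two-group test of PBQ change to 6 months CA (t-test or Mann-Whitney) and, alongside it, linear mixed models in two steps. The step-one model contains only the first allocation (R1). Then: "In the second step we refine the model to take into account both randomization steps, leading to the extended model". The extended model adds the second allocation (R2) as β3 + β13 × time. Time is counted from baseline, and the R2 indicator carries no time subscript. The text describes β2 and β3 as group effects that do not depend on time. On coding, it says: "We will investigate both linear and simple contrasts (comparing each time point with the baseline) in time to assess the treatment effect". It does not say which of these analyses decides the trial.

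On timing, section 2.2.4 (Randomization) says: "One day before discharge to home, participants will be randomized a second time". Section 2.2.3 says: "Outcomes will be assessed at several time points: at baseline; one to two days before discharge to home; at 6 months corrected age", with a further visit at 12 months CA. The PBQ is completed at all four visits, 6 months CA is the primary time point, and baseline assessment precedes the first randomization.

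**The concern.** An allocation that does not yet exist at baseline cannot affect the baseline PBQ. At discharge, post-discharge MT has not begun. The true R2 effect should therefore be zero at the first two visits and can appear only at 6 and 12 months. The extended model does not impose this. With linear time, it forces the effect onto a straight line through all four visits, which cannot be flat at zero and then step up.

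The sample size treats 4 points as the minimal clinically important difference. A true 4-point difference at 6 months that the model reports as 2.7 would look as if it fell short of the trial's own threshold. Because no analysis is named as primary, that estimate is one permitted route to the conclusion.

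The description of β2 and β3 is also wrong. With time zero at baseline and a time-by-group interaction, they are the modelled group differences at baseline. Finally, an infant lost before the second randomization has no R2 value and cannot enter the extended model as written.

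**Working it through.** **The plan's own figure.** Inputs from section 2.2.4 (Power calculation): difference 4 points, SD 8, target power 80% per main effect. On the test level it says: "each tested on a two-sided 2.5% significance level, i.e. 5% with Bonferroni correction for two tests". The stated total before inflation is 155.

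- Per arm: 2 × (2.241 + 0.842)² × (8/4)² = 76.04, so 77, or 154 in total. The exact t-test gives 77.3 per arm, 154.6 in total, i.e. 155.
- Clustering: 155/5 = 31 per country; 155 × (1 + 30 × 0.01) = 201.5, against 203 stated (155 × 1.31 = 203.05).
- Attrition: 203/0.8 = 253.75, so 254, against 250 stated.

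These agree within 3%, so the inputs are taken as they stand. Below, 250 × 0.8 = 200 are analysed.

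**Linear time.** With complete, balanced data and a random intercept, the expected fitted R2 effect is the least-squares line through the true effects at the four visits. Assumed visits: 0, 1.5, 8 and 14 months from baseline. The mean is 5.875, the deviations are −5.875, −4.375, 2.125 and 8.125, and their squares sum to 124.19. At the 6-month visit:

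- weight of the true 6-month effect: 1/4 + 2.125²/124.19 = 0.286
- weight of the true 12-month effect: 1/4 + 2.125 × 8.125/124.19 = 0.389

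For true effects 0, 0, 4 and 4g points, the fitted 6-month effect is 4 × (0.286 + 0.389g). The last column covers ten assumed spacings: equally spaced visits, or weeks with baseline at 26–34, discharge at 35–40, and the 6- and 12-month visits at 66 and 92 weeks PMA.

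| 12-month effect relative to 6-month (g) | Fitted 6-month effect (true 4) | Bias over ten spacings |
|---|---|---|
| 0 (gone) | 1.15 | 70–72% too small |
| 0.5 | 1.92 | 50–53% too small |
| 1 (sustained) | 2.70 | 30–34% too small |
| 1.25 | 3.09 | 20–24% too small |
| 1.5 | 3.48 | 10–14% too small |
| 2 | 4.26 | 5–10% too large |

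The bias is zero at g = (1 − 0.286)/0.389, about 1.83 (1.75–1.88 over the spacings). If only the three visits to 6 months are fitted, the line recovers 0.94–1.00 of the true effect on the week scales and 0.83 with equal spacing. Most of the distortion therefore comes from including the 12-month visit.

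In the sustained case the slope is 4 × (2.125 + 8.125)/124.19 = 0.330 per month. The line then shows 2 − 0.330 × 4.375 = 0.56 points at discharge, before any post-discharge MT.

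A simulation of the sustained case (250 enrolled, 20% lost before 6 months and 10% more before 12, correlation 0.5, 100 runs) gave 2.54 from linear time and 3.80 from categorical visits. The ratio is 0.67.

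**Power of the slope test, sustained case.** SE of the slope = √[(4/200) × 64 × (1 − r)/124.19], which is 0.085 at r = 0.3 and 0.072 at r = 0.5. Power at two-sided 2.5% is about 95% and 99%.

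**Precision of the unbiased analyses.** Take SD 8 at each visit and equal correlation r between visits (both r values are assumed).

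- Change from baseline, simple contrast or direct test: variance = (4/200) × 2 × 64 × (1 − r). At r = 0.3 this is 1.792, SE 1.34; at r = 0.5 it is 1.28, SE 1.13.
- R2 effect set to zero at baseline and discharge, free at 6 and 12 months: variance = (4/200) × 64 × [1 − 2r²/(1 + r)]. At r = 0.3 this is 1.103, SE 1.05; at r = 0.5 it is 0.853, SE 0.92.

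For a 4-point effect, power is 77% against 94% at r = 0.3, and 90% against 98% at r = 0.5.

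**The case against.** The strongest reply is that the plan already contains analyses free of this bias. The direct test of change to 6 months is listed first, and simple contrasts against baseline are planned beside the linear ones. This stands: a reader might infer that every planned analysis misstates the 6-month effect, and that is not so. For these analyses the loss is one of precision, and unconstrained contrasts remain valid.

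A reader might also take a one-third shortfall as a lower limit. The documents do not support that. They give no PBQ course after 6 months, and section 2.3 expects clinical benefits over a longer term. With enough growth the shortfall disappears or reverses.

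Nor does attenuation always mean lost power. In the sustained case the slope test (95% and 99%) does better than the simple contrast (77% and 90%). Power as low as 16–21% for the fitted 6-month effect belongs only to an effect that is gone by 12 months.

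Two further inferences go too far. The plan does not call β2 or β3 the treatment effect; it assigns that role to contrasts in time, so the fault is a wrong description. And early leavers are not lost to the analysis of the first factor, because the step-one model needs no R2 value. They drop out of the extended model only.

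One objection qualifies the remedy. The discharge PBQ is due one to two days before discharge and the second allocation is made one day before, with no order stated. The PBQ is self-rated, so a parent who already knows the allocation could answer differently. Zero at discharge is then not guaranteed under the present procedure.

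**Conclusion.** The point holds in limited form. The extended model allows an R2 effect at two visits where it should be zero: at baseline by design, and at discharge because post-discharge MT has not started, provided the allocation is not yet known.

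The linear-time version does not estimate the 6-month difference. Its bias depends on a course that the documents do not give, ranging from 70–72% too small (effect gone by 12 months) to 5–10% too large (effect doubled). The harm is to the estimate rather than always to power. The change test and simple contrasts escape the bias but have standard errors larger than necessary: 1.34/1.05 = 1.28 times at r = 0.3 and 1.13/0.92 = 1.23 times at r = 0.5.

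These sizes rest on assumed visit times, effect courses and correlations, and on reading SD 8 as the SD of a single PBQ score. The structural fault and the wrong description of β2 and β3 need none of those assumptions.

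**What to change.** - Name as the primary estimates the R1 and R2 differences at 6 months CA from one longitudinal model with visit as a categorical factor. Set the R1 effect to zero at baseline and the R2 effect to zero at baseline and discharge. Infants lost before the second randomization then stay in through their earlier visits, where no R2 value is needed.
- Correct the sentence on β2 and β3: in the models as written, they are group differences at baseline.
- Keep linear time as exploratory.
- State in the site procedure that the second allocation is released only after the discharge questionnaires are complete. This makes the zero constraint at discharge valid.

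The cost is analysis-plan wording and one line of site procedure. No new data are needed. If discharge questionnaires have already been completed with the allocation known, the discharge constraint should be dropped for the primary model or examined in a sensitivity analysis; the baseline constraint is unaffected.
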